#### Analysis methods

Full statistical analysis plan predefining all analyses and patient populations will be in place prior to any comparative analyses according to guidelines.^41^ KARDS will be reported according to the Consolidated Standards of Reporting Trials extension for Non-Inferiority and Equivalence Randomised Trials.^42^ The intention-to-treat (ITT) population will include all randomised participants, and the per-protocol (PP) population will include all participants who received their randomised intervention as intended. Although there is no ‘gold standard’ for non-inferiority trials, outcomes will be analysed primarily for the PP population.^43^ A sensitivity analysis will be conducted for the ITT population.

The primary analysis will report adjusted estimates of treatment effect from multivariable regression of KOOS pain score at 12 months. Statistical significance of KJD non-inferiority relative to KR will be based on a 2-sided likelihood-based test with type 1 error of 2.5% in both tails, adjusted by baseline score and OA severity as fixed effects, and delivery unit as a random effect.^44^ If the 95% confidence interval (CI) for absolute difference in means between KJD and KR lies entirely below or includes the non-inferiority boundary, then there would be insufficient evidence to reject the null hypothesis that KJD inferior to KR. Conversely, if the 95% CI lies entirely above the non-inferiority boundary, there would be evidence to reject the null hypothesis and conclude KJD non-inferior to KR. If non-inferiority demonstrated and KJD appears superior to KR, based on estimated effect and associated CI, statistical significance for superiority will be calculated based on an ITT analysis. Secondary analysis of the primary outcome measure will use multilevel modelling to account for longitudinal data collected over 24 months. Sensitivity analyses will be considered to investigate any impact of surgeon experience on treatment effect estimates.^45^

Reasons for missing data will be examined and primary method to account for missing data will be chosen based on the most reasonable missing data mechanism assumption, with sensitivity analyses to assess robustness of results to different missing data mechanism assumptions.

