Other PROM responses will be transformed into dimension scores, according to scoring manuals, and presented graphically and longitudinally. Standardised area under the curve (AUC) statistics will be compared across treatment groups as an analysis conditional on patient time in the trial. Functional assessments will be reported descriptively, along with joint space width for the KJD group.

Complications will be reported as unique events and unique patients experiencing events. Joint survival will be measured from randomisation to time of further intervention and analysed using the Kaplan-Meier method.

Process evaluation interview data will be analysed using thematic content analysis to identify patterns or themes,^46^ using coding of audio-transcript recordings, adopting the framework method described by Ritchie and Spencer and Pope and Mays.^47 48^ Normalisation Process Theory will be used as a theoretical framework to explore and explain extent of intervention implementation,^49–51^ using the software package NVivo V.12 to manage data and facilitate this process. Interview data and full record of issues raised will be discussed in detail with the Trial Management Group and summarised for oversight committees. Good practice will be shared with other recruiting sites.

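### The per-protocol rule is not limited to the KOOS pain non-inferiority test, so read literally it also governs complications, further intervention, secondary PROMs and cost-effectiveness

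*Protocol article*

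**What the plan says.** All of this is in the protocol article, mostly under Analysis methods.

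- **Populations.** "The intention-to-treat (ITT) population will include all randomised participants", whereas "the per-protocol (PP) population will include all participants who received their randomised intervention as intended". The article does not define the closing qualifier further.
- **Ranking.** After remarking that non-inferiority trials have no gold standard, it says "outcomes will be analysed primarily for the PP population". Then: "A sensitivity analysis will be conducted for the ITT population".
- **Only stated exception.** If non-inferiority is shown and KJD appears superior, "statistical significance for superiority will be calculated based on an ITT analysis".
- **Complications.** "Complications will be reported as unique events and unique patients experiencing events". No population is given.
- **Further intervention.** "Joint survival will be measured from randomisation to time of further intervention and analysed using the Kaplan-Meier method". No population is given.
- **Other PROMs and cost-effectiveness.** Methods are described, including the costs of complications and repeat procedures, again without a population.
- **Deferral.** "Full statistical analysis plan predefining all analyses and patient populations will be in place prior to any comparative analyses".

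The section Secondary outcome measures lists complications, further interventions and cost-effectiveness among the trial's outcomes.

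**The concern.** The reason given for a per-protocol primary analysis belongs to the non-inferiority comparison, where dilution by non-adherence can make two treatments look alike. It does not carry over to a complication table, a Kaplan-Meier curve of further intervention or a cost per QALY. None of those is a non-inferiority test, and in each the patients whose treatment went wrong are part of the answer.

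A per-protocol set also conditions on something that happens after randomisation, and here the opportunity differs by arm. Knee replacement (KR) is delivered in one operation. KJD needs a fixator kept in place and removed under anaesthesia after 6 weeks, so there is more time in which treatment can fall short of what was intended, possibly because of its own complications.

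The Rationale section makes the case for offering KJD depend on its being safe, non-inferior on pain and cost-effective. Selection of this kind could favour KJD on the first and third of those conditions.

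**Working it through.** **1. Does the rule reach the secondary outcomes?** The noun in the ranking sentence is plural and unqualified. Elsewhere, when the article means KOOS pain at 12 months, it calls it the primary outcome measure. Complications, further interventions and cost-effectiveness are listed as secondary outcome measures. One analysis, superiority, is explicitly moved to ITT, and no other is. On the wording alone, the per-protocol rule applies to all of them.

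**2. What would it do to joint survival?** The curve starts at randomisation. Under Randomisation and blinding, randomisation takes place within 6 weeks of planned surgery. Under Intervention (KJD), the frame is removed after 6 weeks. If receipt as intended means completed distraction (an assumption), a KJD patient is counted only after reaching a point up to about 6 + 6 = 12 weeks after time zero. A KJD patient whose distraction was abandoned early for a further intervention would then be missing from the curve meant to show that event.

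**3. Is there a figure in the documents for the size?** The denominator is 172 per arm (Sample size). That figure is not in dispute: margin 8, SD 21, one-sided 2.5% and 90% power give 146 per arm by the t-based calculation, and 146/0.85 = 171.8, so 172.

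The nearest figure on treatment interruption is in the Discussion: in a series of 62 patients, two needed surgery for pin-site infection during distraction.

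- 2/62 = 3.2%
- 0.032 × 172 = 5.5, about 6 patients

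The article does not say that distraction ended in those two patients, so this is not an estimate of the proportion excluded.

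**4. How would the bias behave? (assumed values only)** Let R be the true KJD complication rate, e the share of the KJD arm excluded, and r the rate among those excluded. The per-protocol rate is (R − e·r)/(1 − e). With R = 20%:

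| e | r | Calculation | Per-protocol rate |
|---|---|---|---|
| 5% | 50% | (0.20 − 0.025)/0.95 | 18.4% |
| 10% | 80% | (0.20 − 0.080)/0.90 | 13.3% |
| 15% | 100% | (0.20 − 0.150)/0.85 | 5.9% |

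If r = R the formula returns R, so there is no bias unless the excluded patients differ from the rest. None of R, e or r is given in the documents. The table shows direction and sensitivity, not expected size.

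**The case against.** The strongest reply is that nowhere does the article expressly place complications, further surgery or cost-effectiveness in the per-protocol set. The ranking sentence opens by speaking of non-inferiority trials, the KOOS pain test follows directly, and the one analysis that is not a non-inferiority test, superiority, goes to ITT. Per-protocol for non-inferiority and ITT elsewhere is therefore a natural reading of the intent. Populations are also to be predefined in a statistical analysis plan that is not shown.

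Other passages point the same way. Under Monitoring, the data monitoring committee reviews interim safety data by randomised group, and complications are collected from randomisation. Under Data collection, data up to withdrawal from trial treatment are kept in the analysis. Under Concomitant care and interventions, further intervention is permitted and recorded for everyone, so a later conversion to KR is not evidently a protocol deviation.

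The exclusion mechanism is also uncertain. The per-protocol set turns on receipt of the intervention, not on freedom from complications. A patient with a pin-site infection who completes distraction would stay in.

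Much of this stands, and it limits the claim. It does not remove it. The article does more than stay silent: it defines two populations, ranks them for outcomes generally and names one exception. An analysis plan that follows it literally would put harms and costs in the per-protocol set, and one that does not would depart from the published wording. The passages on interim safety and withdrawal data add a tension that should be resolved in the text.

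**Conclusion.** The point holds as a fault of scope. The per-protocol rule is wider than its justification, and the analyses for which it is least suitable are given no other population. Followed literally, it may bias safety, reintervention and cost-effectiveness towards KJD. This assumes that some KJD patients with interrupted distraction count as not treated as intended, and that they fare worse than those retained. ITT results would still be produced, but as a sensitivity analysis they would not be the headline.

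Two stronger readings should be resisted.

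- **That the plan removes the patients with KJD complications and hides harm.** The documents do not say this. The qualifier is undefined, infection alone does not exclude anyone, and ITT results sit alongside.
- **That 8% to 14% of the KJD arm would be lost.** A reader might multiply the pin-site infection rates of 40% and 70% in the Discussion by the 20% needing intravenous therapy, giving about 14 to 24 of 172. The 40% rate is for external fixation done for other reasons, while the 20% belongs to the KJD literature, so the lower product mixes two populations. Intravenous therapy is also not the same as stopping distraction.

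The size of the bias cannot be derived from the documents. The only nearby figure is about 3%, or about 6 of 172, with the reservation stated above. This is a correction to make before any comparative analysis. It does not challenge the sample size or the use of a per-protocol analysis for the KOOS pain non-inferiority test.

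**What to change.** Change the wording under Analysis methods, and carry it into the statistical analysis plan, as follows.

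1. Limit the per-protocol sentence to the primary KOOS pain non-inferiority analysis, with the ITT result reported beside it.
2. Analyse joint survival and further interventions, secondary PROMs and cost-effectiveness primarily by ITT, with per-protocol as supportive.
3. Report complications in all participants in whom a trial operation was started, by procedure received, with a table by randomised group beside it.
4. State what receipt as intended means in each arm for the purpose of defining the per-protocol set, including how shortened distraction is classified.

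If the analysis plan already does this, the article's sentence need only be brought into line with it. The cost is wording and a little more reporting, with no new data. The KJD results may look less favourable than under a per-protocol analysis.

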**Methods and analysis:**

KARDS is a phase III, multicentre, pragmatic, open-label, individually randomised controlled non-inferiority trial comparing KJD with KR in patients with severe knee OA, employing a hybrid-expertise design, with internal pilot phase and process evaluation. 344 participants will be randomised (1:1) to KJD or KR. The primary outcome measure is the Knee Injury and Osteoarthritis Outcomes Score (KOOS) pain domain score at 12 months post-operation. Secondary outcome measures include patient-reported overall KOOS, Pain Visual Analogue Scale and Oxford Knee Scores, knee function assessments, joint space width, complications and further interventions over 24 months post-operation. Per patient cost difference between KR and KJD and cost per quality-adjusted life year (QALY) gained over 24 months will be estimated within trial, and incremental cost per QALY gained over 20 years by KJD relative to KR predicted using decision analytic modelling.

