#### Trial setting and recruitment

Participants will be recruited from secondary care orthopaedic centres following general practitioner (GP) or specialist referral. Potentially eligible participants will be identified by the attending clinical team from orthopaedic outpatient clinics and theatre lists. Following information provision, patients will be given the opportunity to discuss the trial with their family, friends and healthcare professionals before being invited to participate.

Informed consent will be obtained by the Principal Investigator (PI) or appropriate, delegated, healthcare professional as detailed on the Authorised Personnel Log, in accordance with the principles of Good Clinical Practice and Declaration of Helsinki 1996.

All sites must be able to deliver both KR and KJD. As KJD is not a standard technique used in knee surgery, not all surgeons will have the required experience, and some surgeons may not be in individual equipoise despite there being centre equipoise. A hybrid expertise-based design, where surgeons are categorised into ‘delivery units’ based on experience, addresses both issues.

There are two delivery unit categories based on the interventions surgeons are authorised to perform within the trial: (1) *single delivery units* consist of surgeons authorised to deliver KJD **or** KR, where the surgeon performing the procedure will be chosen after randomisation, depending on the allocation or (2) *dual delivery unit*s, consisting surgeons authorised to deliver KJD **and** KR where a randomised participant may receive either operation by the same surgeon.

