### Statistical considerations and analyses

#### Sample size

Power calculations are based on a non-inferiority hypothesis for the primary outcome measure, KOOS pain score. 344 participants (172 per arm) will have 90% power to demonstrate non-inferiority based on an 8 point non-inferiority margin, assuming an SD of 21 points,^2 35–37^ one-sided 2.5% significance level and 15% dropout rate. The non-inferiority margin was agreed by clinical and patient co-applicants based on being 33% less than the 12 point minimally important difference observed in previous trials,^18 38–40^ clinical co-applicant experience and PPI focus group feedback. No adjustment has been made to accommodate surgeon learning curve since external fixation is a common procedure orthopaedic surgeons frequently do for trauma, and minimum expertise is required for surgeon eligibility.

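### The primary model's delivery-unit random effect cannot carry surgeon variation where different surgeons operate in each arm, so the non-inferiority interval can be too narrow

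*Protocol article*

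**What the plan says.** Under Trial setting and recruitment, the protocol article defines two kinds of delivery unit. In a single delivery unit each surgeon is authorised for only one of the two operations, "where the surgeon performing the procedure will be chosen after randomisation, depending on the allocation". In a dual delivery unit the same surgeon may perform either operation. Under Randomisation and blinding, delivery unit is a minimisation factor, so each unit is meant to contain patients of both arms.

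Under Analysis methods, the primary comparison is a regression of 12-month KOOS pain, "adjusted by baseline score and OA severity as fixed effects, and delivery unit as a random effect". No surgeon term and no treatment-by-unit term is named. The one surgeon-related analysis there is a sensitivity analysis of surgeon experience, which is only to be considered.

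Under Sample size: "344 participants (172 per arm) will have 90% power to demonstrate non-inferiority based on an 8 point non-inferiority margin", "assuming an SD of 21 points", with a "one-sided 2.5% significance level and 15% dropout rate". The section explains why no learning-curve allowance was made. It does not mention clustering by surgeon.

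**The concern.** In a single delivery unit the KJD patients share one surgeon or set of surgeons and the KR patients share another. If results differ between surgeons, outcomes are correlated within surgeon, and that correlation lies within one arm. A random intercept per unit adds the same quantity to both arms and cancels from the difference. The model then treats patients of one surgeon as independent for the treatment contrast, and its standard error is too small.

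In a non-inferiority trial this matters more than usual, because an interval that is too narrow makes it easier to clear the margin when KJD is truly inferior by that margin. The article itself makes surgeon variation plausible. It says that KJD is not a standard knee technique, and it leaves the fixator construct and the KR implant partly to surgeon preference. The sensitivity analysis on experience asks whether the effect changes with experience. It does not model the clustering.

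**Working it through.** **1. Reproducing the stated sample size.** Inputs from Sample size: margin 8, SD 21 (variance 441), one-sided 2.5%, power 90%, dropout 15%.

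n per arm = 2 × 441 × (1.960 + 1.282)² / 8² = 144.8, so 145. Dividing by 0.85 gives 170.6, so 171 per arm or 342 in total, against 344 stated. With 172 × 0.85 = 146.2 evaluable per arm, power is 90.3%. The stated figure is therefore the plain two-sample formula, with no surgeon design effect and no gain from baseline adjustment.

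**2. Variance of the contrast with surgeons nested in arm.** Assumptions, none of them in the article: K units, all single, one surgeon per arm per unit, and surgeon ICC ρ. With 146 evaluable patients per arm:

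Var(KJD − KR) = 2ρ × 441/K + 2(1 − ρ) × 441/146

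Without clustering the variance is 2 × 441/146 = 6.04. The design effect is the ratio of the two, and equals 1 + (146/K − 1)ρ. Power at zero true difference is Φ(8/√Var − 1.96). The last column multiplies only the patient-level part by 1 − 0.4² = 0.84, for an assumed baseline correlation of 0.4.

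| K | ρ | Surgeon part | Patient part | Total | Design effect | Power, no baseline credit | Power, correlation 0.4 |
|---|---|---|---|---|---|---|---|
| 20 | 0.02 | 0.88 | 5.92 | 6.80 | 1.13 | 86.6% | 91.1% |
| 20 | 0.05 | 2.21 | 5.74 | 7.94 | 1.32 | 81.0% | 85.5% |
| 10 | 0.02 | 1.76 | 5.92 | 7.68 | 1.27 | 82.3% | 86.9% |
| 10 | 0.05 | 4.41 | 5.74 | 10.15 | 1.68 | 70.9% | 75.0% |

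If half the patients are in single units, the surgeon part halves. In the same row order, power is then 88.7%, 86.4%, 86.6% and 81.0% without baseline credit, and 93.0%, 90.8%, 91.1% and 85.5% with correlation 0.4.

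**3. Error rate of the planned model.** If the standard error ignores the design effect (DE), the one-sided error at a true difference of −8 is about Φ(−1.96/√DE): 3.2%, 4.4%, 4.1% and 6.5% for the four rows. Simulating an analysis with only a delivery-unit random intercept gave:

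- all units single: 3.4% to 4.9% with 20 units and 4.1% to 6.8% with 10 units, over ρ = 0.02 to 0.05;
- half the units single: 2.8% to 4.8%;
- all units dual: about 2.5%, because the surgeon effect is then shared by both arms;
- an analysis of arm differences at unit level, which allows arm-specific effects: about 2.5%.

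**4. Baseline adjustment does not repair the error rate.** It reduces patient-level variance and leaves surgeon variance in place. At ρ = 0.05 and correlation 0.4 the residual surgeon ICC becomes 0.05/(0.05 + 0.95 × 0.84) = 0.059, slightly higher than before.

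**The case against.** Five points can be made for the plan.

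- **Expertise-based design.** The hybrid design is deliberate, so the surgeon is part of the treatment as delivered. A reader might infer that surgeon is confounded with treatment and that the estimate is biased. The documents do not support that: the issue is the width of the interval, not the point estimate. It can be argued that inference is meant only for the participating surgeons. If so, the plan should say so. Its stated aim, to decide whether KJD could be offered routinely in the NHS, points the other way.
- **Power.** A reader might infer that the trial falls short of 90%. That does not follow. The calculation takes no credit for adjusting for the baseline score, and a correlation of 0.4 would restore 90% or more in several of the scenarios above, though not in all.
- **Size.** Dual units are unaffected, and more surgeons per arm dilute the effect. At 3 patients per surgeon and ICC 0.01 the design effect is 1.02 and power is 89.7%. Nothing in the article shows that KJD cases will be concentrated on few surgeons. This stands, and every magnitude here is conditional.
- **Unseen analysis plan.** A full plan is promised and may add terms. But the article does state the random effect of the primary test, so this is a stated rule and not a detail left open.
- **Cost of the remedy.** In the simulation with 20 units and 7 patients per arm in each, the unit-level analysis had 86% power when surgeon variance was nil, against 90% for the shared intercept. This stands as a real price.

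**Conclusion.** The structural point holds for single delivery units. The primary model as stated has no term for surgeon variation within arm. With any surgeon ICC above 0 and more than one patient per surgeon, its interval is too narrow, in the direction of falsely declaring non-inferiority. Under the assumed 10 to 20 units, one surgeon per arm per unit and ICC 0.02 to 0.05, the nominal 2.5% becomes about 3.4% to 6.8% with all units single and 2.8% to 4.8% with half single. It stays nominal with all units dual.

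The 90% power may be optimistic, but a shortfall is not shown. For all single units the range is about 71% to 87% without baseline credit and 75% to 91% with an assumed correlation of 0.4. The ICC, caseload, unit mix and baseline correlation all lie outside the document.

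**What to change.** Add to the primary model either a random effect for surgeon or a random treatment-by-delivery-unit term, with a small-sample degrees-of-freedom correction. Keep delivery unit, baseline score and OA severity. Because the Eligibility section lets surgeons operate under direct consultant supervision, define in advance whether the operating surgeon or the responsible consultant forms the cluster. If the omission is intended, justify it by naming the surgeons to whom the inference applies.

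Restate the power as conditional on surgeon ICC, patients per surgeon, the single/dual mix and the baseline correlation, over a plausible range.

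No extra patients or visits are needed to change the model, and it can be fixed before any comparative analysis, provided that the surgeon is recorded for each operation. The cost is a somewhat wider interval, some loss of power even if surgeons do not differ, and possibly a less favourable stated power.

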#### Data collection

Clinical data will be collected at baseline, day of surgery, prior to discharge, week 6 (KJD only), and months 3, 12 and 24 post-surgery. Participant completed data will be collected at baseline, day of surgery and months 3, 6, 12 and 24 post-surgery. Full assessment schedule based on the Standard Protocol Items: Recommendations for Interventional Trials (SPIRIT) guidance is^24^ provided in online supplemental material 1.

10.1136/bmjopen-2022-062721.supp1Supplementary data

Participating sites will maintain a file of essential trial documentation including copies of all completed Case Report Forms (CRFs). Sites will post paper CRFs and electronically transfer trial X-rays to Leeds CTRU. Trial data will be entered onto an electronic database, except post-surgery questionnaires completed using electronic remote data capture by participants or via postal questionnaire.

Data will be monitored for quality and completeness by CTRU. Missing data will be requested from sites until received, confirmed as unavailable or trial analysis begins. The sponsor reserves the right to conduct periodic source data verification to monitor trial integrity.

Participant qualitative interviews will be conducted by telephone, and staff interviews conducted in person or telephone/video conference. Interviews will be audio recorded on an encrypted recorder, anonymised and transcribed verbatim for analysis.

All information collected during the trial will be kept strictly confidential. Information will be held securely on paper and electronically at Leeds CTRU, with process evaluation data held securely on Warwick Clinical Trials Unit (CTU) server. Both will comply with all aspects of the Data Protection Act 2018. If a participant withdraws consent from further trial treatment and/or further data collection, data to the point of withdrawal will remain on file and included in the analysis.

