##### Secondary outcome measures

*Patient report outcome measures (PROMs) and QoL within 24 months post-surgery*
KOOS (overall and at component level).Pain Visual Analogue Scale (VAS).^26 27^Oxford Knee Score (OKS). 28–30
*Objective assessment of knee function*
Active range of movement.Timed-up-and-go test.^31 32^
*Incidence of complications, including infection*
Intra-operative complications.Post-operative complications.^33^
*Further interventions within 24 months postsurgery*
Further surgical interventions including conversion to KR or revision surgery.
*KJD’s potential as cartilage regenerative therapy*
Joint space width (assessed using standardised fixed flexion PA at 20^o^ X-rays^34^).
*Estimate of short-term and long-term cost-effectiveness*
EuroQol 5 Dimensions (EQ-5D)-3L questionnaire at 24 months.Health Resource Utilisation and Private Costs questionnaire at 24 months.Incremental costs per QALY gained at 20 years.Implementation processes and intervention fidelityQuantitative (surgical CRF and central review of post-operative X-rays).Qualitative evaluation with surgical and clinical staff.Qualitative evaluation of participant experiences.

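### Comparing the other PROMs by an AUC conditional on time in the trial can mix treatment effect with follow-up length when scores change over time and dropout differs by arm in amount or timing

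*Protocol article*

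**What the plan says.** In Analysis methods, the article says that the other PROMs will be scored by their manuals and shown graphically over time. It then gives one between-arm comparison for them: "Standardised area under the curve (AUC) statistics will be compared across treatment groups as an analysis conditional on patient time in the trial". It does not define *standardised*, and it does not say how the AUC is formed for someone who leaves before month 24.

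Secondary outcome measures lists KOOS (overall and by component), pain VAS and OKS under "Patient report outcome measures (PROMs) and QoL within 24 months post-surgery". Data collection gives the schedule: "Participant completed data will be collected at baseline, day of surgery and months 3, 6, 12 and 24 post-surgery".

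KOOS pain is treated differently: "Secondary analysis of the primary outcome measure will use multilevel modelling to account for longitudinal data collected over 24 months". Analysis methods also has a general missing-data paragraph, in which the method follows the most plausible mechanism and sensitivity analyses are added. That paragraph comes after the primary-outcome text and is not tied to the AUC. The only dropout figure is the overall one under Sample size: "one-sided 2.5% significance level and 15% dropout rate".

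**The concern.** Dividing an AUC by the time observed gives a mean score per unit time, but not the same mean for everyone. After surgery for severe knee OA, scores are expected to rise during recovery and then level off. Someone last seen at month 3 is averaged over the steep part only, whereas a completer's average is mostly plateau. The two values look alike and enter the comparison as if they measured the same thing.

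Time in the trial is itself observed after randomisation, and the trial is open-label. The early experience also differs between arms, since only KJD involves about 6 weeks in an external fixator and a removal procedure. Differential dropout is therefore plausible, although nothing in the article predicts its size or direction. If it occurs, part of the PROM contrast reflects who stayed and for how long. An early leaver also receives a complete-looking value, so the gap is hidden rather than handled.

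**Working it through.** **The plan's own figure.** The article gives no figure for the AUC analysis. Its one relevant calculation is the sample size: "344 participants (172 per arm) will have 90% power to demonstrate non-inferiority", "based on an 8 point non-inferiority margin, assuming an SD of 21 points". With n = 2 × SD² × (1.960 + 1.282)² / margin² = 2 × 441 × 10.51 / 64, the result is 145 evaluable per arm. Dividing by 0.85 gives 171 per arm, or 342 in total, against 344 stated. It reproduces closely and is not affected by this point.

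**Inputs.**
- From the article: visits at months 3, 6, 12 and 24, plus a preoperative value taken as month 0; 15% dropout overall.
- Assumed: *standardised* means trapezoid AUC divided by time to last visit; mean course 40, 60, 70, 78, 80 at months 0, 3, 6, 12, 24 in both arms, on a 0–100 scale where higher is better, as for KOOS; arm-specific dropout.

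**Step 1: one participant, different last visits.**
- Month 3: 3 × (40 + 60)/2 = 150; 150/3 = 50.0
- Month 6: 150 + 3 × (60 + 70)/2 = 345; 345/6 = 57.5
- Month 12: 345 + 6 × (70 + 78)/2 = 789; 789/12 = 65.75
- Month 24: 789 + 12 × (78 + 80)/2 = 1737; 1737/24 = 72.375

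The shortfall against a completer is 22.375, 14.875 or 6.625 points.

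**Step 2: spurious difference with no true effect.** Shift = excess dropout × shortfall.

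| Excess dropout in one arm | Leave after month 3 | Month 6 | Month 12 |
|---|---|---|---|
| 5 percentage points (e.g. 17.5% v 12.5%) | 1.1 | 0.7 | 0.3 |
| 10 percentage points (e.g. 20% v 10%) | 2.2 | 1.5 | 0.7 |

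Both examples keep the overall rate at 15%. The arm with more dropout looks worse.

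**Step 3: other course shapes, 10-point excess.**
- 40, then 75 from month 3 onward: 1.5, 0.7, 0.2
- 40/65/75/75/65: 1.7, 0.8, 0.1
- Flat throughout: 0, 0, 0

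**Step 4: equal dropout, different timing.** With 15% leaving in each arm, after month 3 in one and after month 12 in the other, the main course gives 0.15 × (50.0 − 65.75) = −2.4 points. With the same course, amount and timing in both arms, the shift is 0.

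**Scale.** If the SD of 21 for KOOS pain carried over and all 172 per arm contributed, the standard error of the difference would be 21 × √(2/172) = 2.26. A shift of 1.1 is then about half a standard error, and 2.2 about one. Using 1 − Φ(1.96 − b/SE) + Φ(−1.96 − b/SE), a two-sided 5% test would reject about 8% of the time at b = 1.12 and about 17% at b = 2.24.

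**The case against.** The strongest reply is that the article discloses what it does. It calls the analysis conditional on time in the trial, and a while-in-trial average is biased only against a full 24-month contrast. But the same article defines these outcomes over 24 months, so the summary and the outcome do not match. Disclosure does not remove that.

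Second, *standardised* is undefined, and the full analysis plan, not shown here, may define it harmlessly. This stands as a limit on certainty: the point depends on a reading, though the natural one given the words beside it.

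Third, the missing-data paragraph is not worded as limited to the primary outcome, and the PROMs will be displayed over time. Both help, but neither is tied to the AUC comparison, and conditioning on observed time leaves nothing visibly missing to handle.

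Fourth, a mixed model is no complete cure. That is right: it removes dropout bias only if data are missing at random, which an open-label trial does not guarantee.

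A reader might also infer that the comparison is biased whenever dropout differs by arm. The working does not support that. A flat course gives no bias and late dropout gives little, while equal dropout with different timing can bias too.

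**Conclusion.** The point holds in a conditional form. If *standardised* means divided by own follow-up time, the stated comparison is biased against the 24-month outcome when scores change over time and dropout differs between arms in amount or timing. On the assumed rising course, the shift runs from 0.3 to 1.1 points for a 5-point excess of dropout and from 0.7 to 2.2 points for a 10-point excess, depending on when leavers are last seen.

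The article gives no PROM trajectories and no dropout by arm, so these are illustrations rather than forecasts, and they refer to a 0–100 scale. It would be tempting to conclude that the trial's main result is at risk. It is not: the 12-month KOOS pain non-inferiority analysis and the sample size do not use this AUC, and the QALY analysis has its own AUC with baseline adjustment and imputation. The change is worth making for the secondary PROMs because the better method is already in the plan for another outcome.

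**What to change.** - Define *standardised*, and compare every PROM over a common 0–24 month window.
- Fit to each PROM the multilevel repeated-measures model already planned for KOOS pain, with baseline score, OA severity, delivery unit, time and treatment-by-time.
- Take the AUC as a fixed linear contrast of the fitted visit means. The trapezoid weights for months 0, 3, 6, 12 and 24 are 1.5, 3, 4.5, 9 and 6, each divided by 24. On the course above they return 72.375 for everyone.
- State the missing-at-random assumption, and extend the missing-data sensitivity analyses already planned to these outcomes.
- Keep the patient-level conditional AUC as descriptive or supportive.

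The cost is a wording change and a little more analysis work, with no new data. The price is open reliance on missing at random, which the sensitivity analyses should probe.
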